### Outcome assessment

#### Primary outcomes

The main outcome will be the difference before and after intervention in the percentage of participants meeting recommended levels of PA (at least 150 minutes at week of moderate to vigorous intensity) [1,2], between and within intervention and control groups. Based on previous experiences [20-23], the PA program (intervention) will be considered effective if it achieves an increase of 20% in the proportion of hypertensive patients in the intervention group defined as active compared to control group, at the end of the intervention (24 weeks) to evaluate adherence and at 32 weeks to assess the sustainability of intervention effects.

PA levels will be assessed at three time points during the study to determine changes in the following: percentage of participants meeting the PA recommendation, minutes of moderate and vigorous PA performed per week and minutes per day of sedentary behavior. In the intervention group, we will also measure change over time in the following tests of functional capacity: walking distance (6 minute walk test) [37], maximum heart rate and 1 minute heart-rate recovery [38]; these measurements will be taken at baseline, 24 and 32 weeks too. These variables will be used as a complementary assessment of participant’s functional capacity and not as the primary outcome of the study.

#### Secondary outcomes

Outcomes assessed in the intervention and control groups at 24 and 32 weeks will be: a) blood pressure levels; b) biochemical markers: triglycerides, total cholesterol and HDL, fasting glucose; c) anthropometric measures: weight, BMI, hip and waist circumference to calculate waist/hip ratio; d) social/psychological measures: attitude towards PA participation based on Prochaska’s stages of change model [29], PA self-efficacy [39] health related quality of life (SF-12) [40], symptoms of depression (CESD, 20-item version) [41] and social support for PA participation.

### Measurements

Several kinds of data will be collected to measure the intervention’s effects. Measurement procedures are described here:

#### Physical activity measurement

Amount of PA will be measured with objective and self-report instruments.

Objective: Participants will be monitored via ActiGraph GT3X accelerometers (ActiGraph LLC, Ft. Walton Beach, Florida) while exercising. This device has an internal time clock and extended memory, and is able to record and store the magnitude of acceleration and deceleration of movements. The recorded data is scored as a “count”, which can be summed in a specific time interval called an “epoch”. In this study, an epoch will equal sixty seconds. Participants will be instructed to wear the device for 7 days during all waking hours, and to remove it only during swimming, bathing or other contact with water. The accelerometers will be mounted on elastic belts and placed at the right hip. For this study the wear time will be valid, if the patient wears the device for 5 days in one week (including at least 1 weekend day) to accumulate at least 600 minutes daily.

Each patient’s accelerometer record will be analyzed in terms of time (in minutes) performing moderate to vigorous PA per day, to calculate the average time spent (in minutes) of PA during the week. Using this data, we will categorize patients as complying or not complying with recommended levels of PA [2], (150 minutes of PA moderate to vigorous intensity at week) at the different measurement points (baseline, 24 and 32 weeks to IG and baseline and 24 weeks to CG) during the study.

Self-report instrument: PA levels during leisure time will be measured with the short version of the International Physical Activity Questionnaire (IPAQ) [28]. The IPAQ will be used to confirm the patients’ PA levels at screening and at the study measurement points, and will be complemented with a physical activity logs that participants will complete every week and deliver to the research team monthly.

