**Methods and design:**

We will describe the methods of a cluster randomized trial study designed to evaluate the effectiveness of an exercise referral scheme to increasing physical activity in hypertensive patients compared to a non-referral scheme. Four PHCU were selected for the study; the PHCU will take part as the unit of randomization and sedentary hypertensive patients as the unit of assessment. 2 PHCU of control group (GC) will provide information to hypertensive patients about physical activity benefits and ways to increase it safely. 2 PHCU of intervention group (IG) will refer patients to sports facilities at the same institution, to follow a group-based PA program developed to increase the PA levels with a designed based on the Transtheoretical Model and Social Cognitive Theory. To evaluate the effects of the intervention as well as short-term maintenance of the intervention’s effects, PA will be assessed at baseline, at 24 and 32 weeks of follow-up.

The main outcome will be the difference before and after intervention in the percentage of participants meeting recommended levels of PA between and within intervention and control groups. PA will be measured through self-report and with objective measure by accelerometer.

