### Control group (CG)

Participants in the control group will be informed about health benefits of PA and a balanced diet, and how to safely increase PA levels. Patients in this group will continue receiving their usual care at PHCU facilities. The control group will be invited to undergo two subsequent PA assessments at the PHCU facilities at 24 and 32 weeks of follow-up. The research team will keep in contact with these patients during monthly doctor’s appointment or through a monthly phone call to emphasize the participation in the study and with appointment reminders at weeks 22 and 30.

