### Statistical analysis

Analysis of effectiveness will be carried out according to an intention to treat analysis.

A baseline comparability analysis will be carried out among the IG and CG, in relation to the variables studied during the three measurement points in the study (0, 24 and 32 weeks). To compare means, T-test or analysis of variance will be conducted, while Mann–Whitney tests will be used to compare variables without a normal distribution. Analysis of covariance will be conducted to assess variables with repeated measures along the study.

Longitudinal generalized mixed models will be developed to account for the repeated measurements (0, 24 and 32 weeks) for each patient. These models will be linear for continuous changes in PA (minutes), and logistic for categorical PA variables.

For the primary outcome variable, models will be adjusted for potential confounding variables that may alter the proportion of patients who meet the minimum recommendation for PA: a) geographic accessibility barriers (e.g. distance to SCC); b) financial (e.g. self-report of financial resources to pay for transportation); c) administrative (e.g. SCC schedules not being compatible with patient’s reported schedules); d) social support (e.g. help with transportation to the SCC); e) conditions of patient (for example: greater physical fitness than other hypertensive patients, discomfort or injury discouraging participation in the program, presence of acute or chronic diseases).

In order to minimize regression bias to the estimated mean, baseline values for each dependent variable will be included in each regression model [47].

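### As written, controls wear no accelerometer at 32 weeks, so the 32-week effectiveness criterion cannot be evaluated on the objective measure

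*Protocol article*

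**What the plan says.** Under Physical activity measurement, the accelerometer record is turned into the binary outcome: "Using this data, we will categorize patients as complying or not complying with recommended levels of PA". The same sentence gives the times at which this is done: "baseline, 24 and 32 weeks to IG and baseline and 24 weeks to CG". It is the only place in the article that sets accelerometer time points by arm. The self-report paragraph of that section puts the IPAQ at screening and at the study measurement points, with no exception for controls.

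Primary outcomes defines success as an "increase of 20% in the proportion of hypertensive patients in the intervention group defined as active compared to control group", and sets the times: "at the end of the intervention (24 weeks) to evaluate adherence and at 32 weeks to assess the sustainability of intervention effects". The abstract names both instruments for the main outcome and gives one schedule for everyone: "PA will be assessed at baseline, at 24 and 32 weeks of follow-up".

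Two further sections describe three time points. Control group (CG) says: "The control group will be invited to undergo two subsequent PA assessments at the PHCU facilities at 24 and 32 weeks of follow-up". Statistical analysis plans longitudinal mixed models to "account for the repeated measurements (0, 24 and 32 weeks) for each patient".

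**The concern.** The success criterion at 32 weeks is a comparison between arms, and one arm has no accelerometer data at that time under the measurement section. The criterion and the schedule cannot both be carried out on the objective measure.

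The stake is the trial's claim about maintenance. The Background faults earlier referral studies for showing effects by self-report only and offers this trial as the one that measures effectiveness objectively. The Discussion repeats that claim. Under the schedule as written, two kinds of evidence are left at 32 weeks. One is a controlled comparison on self-report. The other is an uncontrolled change over time on the device in the intervention arm, which cannot separate a lasting effect of the programme from any change that would have occurred anyway.

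**Working it through.** No published figure is in dispute here, so the check is to set the sections side by side and count the records each arm would supply.

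**Schedule by section**

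| Section | Arms | Times (weeks) | Instrument |
|---|---|---|---|
| Abstract, Methods and design | no distinction | 0, 24, 32 | self-report and accelerometer |
| Control group (CG) | control | 24, 32 after baseline | not named |
| Primary outcomes, criterion | intervention vs control | 24, 32 | not named |
| Physical activity measurement, accelerometer | intervention | 0, 24, 32 | accelerometer |
| Physical activity measurement, accelerometer | control | 0, 24 | accelerometer |
| Physical activity measurement, IPAQ | no distinction | study measurement points | self-report |
| Statistical analysis | each patient | 0, 24, 32 | not named |

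The control row for the accelerometer is the only one that lacks 32 weeks. It directly opposes the abstract (both instruments, three times) combined with the Primary outcomes criterion. The Control group and Statistical analysis sections name no instrument. They could be satisfied by the IPAQ alone, so they neither cure the gap nor contradict it outright.

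**Records available at 32 weeks**

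Inputs from Sample size: 112 enrolled per arm, 40% loss allowed for, 68 completers per arm intended.

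- Expected completers per arm: 112 × (1 − 0.40) = 67.2, about 67, close to the intended 68.
- Accelerometer: about 67 intervention, 0 control.
- IPAQ: about 67 in each arm.

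The target of 68 serves here only as a count of completers. Whether it follows from the stated power and significance level is a separate question, and the point does not depend on it.

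**What the criterion needs**

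Let D(32) = p_IG(32) − p_CG(32), where p is the proportion meeting the recommendation. Sample size describes the aim as a move from 17% to 37%, so the 20% is read as 20 percentage points, and success requires D(32) ≥ 20 points.

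Suppose the intervention arm reaches the planned 37% on the accelerometer at week 32. The criterion is then met only if p_CG(32) ≤ 37% − 20% = 17%. With no control records, p_CG(32) could be anything from 0% to 100%, so D(32) could lie anywhere from 37 − 100 = −63 to 37 − 0 = +37 points. The data cannot show on which side of 20 points it falls.

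**Can the model fill the gap?**

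A mixed model tolerates patients with missing visits, but it borrows from other patients in the same arm at the same visit. Here there would be none. A 32-week arm contrast could be obtained only by imposing a shape on the control trajectory, for instance that it stays at its week-24 level. That is an assumption, and the trial would hold no accelerometer data with which to test it.

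**The case against.** The strongest reply is that this is a slip in one parenthesis. The abstract, the control-group section, the outcome definition and the analysis section all read as a common three-point schedule, and Figure 2, which might settle the matter, is not available here. That is a fair reading, and the true intention is uncertain. It does not remove the problem: the parenthesis names each arm separately, it is the only device schedule given by arm, and staff who follow it would issue no accelerometers to controls at week 32.

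A second reply is that the criterion can still be evaluated. Primary outcomes does not demand the accelerometer at each time. The 24-week comparison keeps both arms on both instruments, and the IPAQ covers 32 weeks. This stands, and it limits the point to the objective comparison of short-term maintenance. But a reader of the abstract and Background would expect that comparison to be objective, and nothing in the article says otherwise.

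Third, the biases in a comparison within the intervention arm should not be overstated. No recruitment calendar is given, so a seasonal effect is possible but not shown. Patients are selected as inactive by IPAQ, not by accelerometer, so regression to the mean on the device would be indirect, and the plan adjusts for baseline values. These points also stand. The conclusion does not need either bias, because without controls the arm difference is simply not observed.

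**Conclusion.** The concern holds. If the accelerometer schedule is followed as written, there are 0 control records at 32 weeks against about 67 in the intervention arm, and the 32-week between-arm criterion is not estimable on the objective measure without extrapolating the controls from week 24. The finding is confined to that one comparison: the 24-week result on either instrument and the 32-week result on the IPAQ are unaffected.

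The count of 67 assumes the planned enrolment and the planned 40% loss; the zero depends on neither. The conclusion assumes that the 32-week control assessment, for which no instrument is named, does not include the device. If it was meant to, the measurement section is wrong and needs correcting. The matter needs settling before controls reach week 32, because the missing records cannot be obtained afterwards.

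**What to change.** Confirm which schedule is intended, then make one of two changes.

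1. **Same device schedule in both arms.** In Physical activity measurement, give baseline, 24 and 32 weeks for intervention and control alike. In Control group (CG), say that the 32-week assessment includes the seven-day accelerometer wear. The cost is about 67 further wears. The control assessment at week 32 is already planned, but each device must be issued and returned about a week apart, so some extra contact is needed. The article does not say how many accelerometers there are; this option assumes enough are available.

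2. **Narrow the claim.** If devices are short, add a sentence to Primary outcomes stating that the controlled 32-week comparison rests on the IPAQ alone, and that 32-week accelerometer data in the intervention arm are descriptive. Make the abstract, Discussion and Statistical analysis agree, with no 32-week arm contrast reported from the accelerometer model. This costs only text, but it gives up objective controlled evidence on maintenance.

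The first option is preferable because it keeps the objective comparison on which the trial's rationale rests.

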### Clinical measurements

#### Biochemical markers

1) Blood pressure levels: will be measured with a digital instrument following criteria established by the JNC 7 [27]; 2) Fasting glucose levels: blood samples will be taken following a fasting period of at least of 8 hours. The serum glucose determination will be made using the enzymatic calorimetric method. All blood biochemistry tests, including total cholesterol, high density lipids (HDL), and triglycerides will be conducted with a Selectra XL (Randox) in accordance with the procedures of the International Federation of Clinical Chemistry and Laboratory Medicine [42].

#### Anthropometric measurements

Will be carry out by trained nurses, following standard procedures: 1) Weight: will be measured with a TANITA electronic scale, with participants wearing minimal clothes and without shoes; 2) Height: will be measured with a conventional stadiometer, with participants standing without shoes; 3) Body Mass Index (BMI): will be calculated by dividing kilograms by height in meters squared. The data obtained will be categorized according to the following criteria: normal (BMI = 18.5-24.9 kg/m^2^), overweight (BMI = 25–29.9 kg/m^2^) and obese (BMI = ≥ 30 kg/m^2^) [43] 4). Waist circumference: measured at the highest point of the iliac crest at the end of expiration, to the nearest measuring tape point of 0.1 cm. The criteria for abdominal obesity will be: men > 100 cm and women > 88 cm [44] 5); Hip circumference: Participants will be standing with feet separated about 20 cm and weight distributed evenly on both feet, at level of the maximum extent of gluteus in a horizontal plane, verifies that the measuring tape covers at same high the perimeter of the body, near to the skin but without compress [45].

### Demographic, health history and lifestyle measurements

At the three measurement points of the study, participants will complete questionnaires asking about sex, age, marital status, highest educational level, household income; their current, past and family history of hypertension, history of other chronic conditions and diseases, current pharmacological treatments, food intake, tobacco and alcohol consumption. In addition, participants’ attitudes toward behavior change based on Prochaska’s stages [29] and self-efficacy regarding PA behavior change [35,36,39]. Health-related quality of life (SF-12) [40], symptoms of depression (CES-D) [41] and social support will be assessed. Sections of the questionnaire (variables that could change between measurements), will be applied at the study’s three measurement points, to both the control and intervention groups.

### Data management

All the information provided by participants will be supervised by the research team, and also by independent researchers. Questionnaires and clinical test results will be directly captured in a customized Microsoft Access database at the time of the interview with the participant and at the delivery of clinical test results to the patient. Information from other sources (daily PA, attendance record) will also be captured in the customized Microsoft Access database.

### Statistical analysis

Analysis of effectiveness will be carried out according to an intention to treat analysis.

A baseline comparability analysis will be carried out among the IG and CG, in relation to the variables studied during the three measurement points in the study (0, 24 and 32 weeks). To compare means, T-test or analysis of variance will be conducted, while Mann–Whitney tests will be used to compare variables without a normal distribution. Analysis of covariance will be conducted to assess variables with repeated measures along the study.

Longitudinal generalized mixed models will be developed to account for the repeated measurements (0, 24 and 32 weeks) for each patient. These models will be linear for continuous changes in PA (minutes), and logistic for categorical PA variables.

For the primary outcome variable, models will be adjusted for potential confounding variables that may alter the proportion of patients who meet the minimum recommendation for PA: a) geographic accessibility barriers (e.g. distance to SCC); b) financial (e.g. self-report of financial resources to pay for transportation); c) administrative (e.g. SCC schedules not being compatible with patient’s reported schedules); d) social support (e.g. help with transportation to the SCC); e) conditions of patient (for example: greater physical fitness than other hypertensive patients, discomfort or injury discouraging participation in the program, presence of acute or chronic diseases).

In order to minimize regression bias to the estimated mean, baseline values for each dependent variable will be included in each regression model [47].

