### Design and recruitment process

This is a cluster randomized trial, with the primary health care unit (PHCU) as the unit of randomization and hypertensive patients as the unit of assessment, to evaluate the impact of a PA-referral scheme to help patients increase their PA levels and meet recommended PA guidelines. Four MSSI PHCU facilities will be assigned in a randomized way to intervention (2 PHCUs) and control groups (2 PHCUs). In all PHCUs, primary care physicians will identify hypertensive patients based on the following criteria: women and men with MSSI affiliation, between 35 and 70 years old, less than 5 years from hypertension diagnosis and/or without pharmacological treatment self-reporting willingness to engage in a PA program but currently not meeting PA recommendations (< 150 minutes per week of moderate to vigorous intensity PA). Using a standardized protocol, physicians will quickly screen for these criteria and will refer eligible patients to the study suite, located in the same PHCU facility. Trained staff will verify that potential participants meet the inclusion criteria described below, to confirm that they can safely engage in the PA program.

Inclusion criteria:

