### Randomization

Randomization will be performed before other study activities, and conducted at MSSI facilities outside the PHCUs to avoid contamination. The 4 PHCUs were randomized into the intervention group (IG; 2 centers) and control group (CG; 2 centers) using sealed envelopes by a health researcher who was not involved in this study. To avoid contamination, that PHCUs selected, are on average 5.5 kilometers (kms) from the place where patients will be referred (IG at 5.1 kms. and CG at 6.6 kms.), within the urban area of the city and public transportation available, average transfer time is 20 to 30 minutes.

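### Four PHCUs are randomised but the stated analysis treats patients as independent, so p-values and confidence intervals for the referral effect are too optimistic

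*Protocol article*

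**What the plan says.** The Design and recruitment process section fixes the design: "This is a cluster randomized trial, with the primary health care unit (PHCU) as the unit of randomization". The Randomization section gives the number of units: "The 4 PHCUs were randomized into the intervention group (IG; 2 centers) and control group (CG; 2 centers) using sealed envelopes".

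The Statistical analysis section then describes three things.

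- The main models: "Longitudinal generalized mixed models will be developed to account for the repeated measurements (0, 24 and 32 weeks) for each patient". They are linear for minutes of activity and logistic for categorical activity variables, and the baseline value of each dependent variable is included.
- Simpler comparisons: "To compare means, T-test or analysis of variance will be conducted, while Mann–Whitney tests will be used to compare variables without a normal distribution". The section also adds an analysis of covariance for repeated measures.
- Covariates for the primary outcome: "models will be adjusted for potential confounding variables that may alter the proportion of patients who meet the minimum recommendation for PA". The list covers distance and other access barriers, money for transport, schedules, social support and the patient's condition. PHCU is not on it.

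The Sample size section compares 17% with 37%, gives 68 patients per group and raises this to 112 for dropout. It contains no ICC and no design effect.

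**The concern.** When whole PHCUs are allocated, patients attending the same PHCU share staff, catchment and access, and their outcomes are correlated. The variance of the arm difference then has a between-PHCU part that does not shrink as more patients per PHCU are enrolled. A model with only a patient-level random effect leaves that part out, so its standard errors are too small and its type I error exceeds 5%.

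Two PHCUs per arm is close to the smallest possible cluster design. A chance difference between two pairs of clinics is easily mistaken for an effect of referral. The Primary outcomes section sets a 20% gain over control as the mark of effectiveness, and the abstract says the findings will guide decisions in Mexico and Latin America, so the error falls on the main conclusion.

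The exercise classes in the intervention arm (6 to 8 groups of 5 to 20 patients, Implementation section) may add a second layer of correlation in that arm only. This is secondary.

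**Working it through.** **Inputs from the article.** Four PHCUs, two per arm; 17% versus 37%; 68 evaluable and 112 enrolled per arm. Assuming equal PHCU sizes, m = 68/2 = 34 or 112/2 = 56 patients per PHCU. **Assumed:** ICC of 0.005 to 0.05, because the article gives none.

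**The plan's own figure.** For two independent proportions, n = [z_α√(2p̄q̄) + z_β√(p₁q₁ + p₂q₂)]²/d², with p̄ = 0.27 and d = 0.20. Two-sided at 90% power: (1.960 × 0.628 + 1.282 × 0.612)²/0.04 ≈ 101.5, so 102 per group. One-sided, it is 83. The stated 68 is not reproduced; that is a separate matter. What counts here is that the stated calculation makes no allowance for clustering.

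**Type I error of a patient-level test.** The design effect is DE = 1 + (m − 1) × ICC, and the actual two-sided error is 2[1 − Φ(1.96/√DE)]. Example: m = 34, ICC 0.01 gives DE = 1 + 33 × 0.01 = 1.33, √DE = 1.15, and error 2[1 − Φ(1.70)] = 8.9%.

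| ICC | DE (m = 34 / 56) | SE understated by a factor of | Actual error of a nominal 5% test |
|---|---|---|---|
| 0.005 | 1.17 / 1.27 | 1.08 / 1.13 | 6.9% / 8.3% |
| 0.01 | 1.33 / 1.55 | 1.15 / 1.24 | 8.9% / 11.5% |
| 0.02 | 1.66 / 2.10 | 1.29 / 1.45 | 12.8% / 17.6% |
| 0.05 | 2.65 / 3.75 | 1.63 / 1.94 | 22.9% / 31.1% |

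A beta-binomial simulation (200,000 trials, 17% in both arms, pooled z-test) agrees: 8.8%, 12.9% and 22.9% for m = 34, and 11.7%, 17.9% and 31.6% for m = 56, at ICC 0.01, 0.02 and 0.05. In the same runs a t-test on the four PHCU proportions with 2 df stayed between 4.8% and 5.1%.

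**Width of an interval that respects the design.** The 2-df critical value is 4.30, so the width ratio is √DE × 4.30/1.96.

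- m = 34, ICC 0.01: the patient-level SE is √(0.3742/68) = 0.0742, where 0.3742 = 0.17 × 0.83 + 0.37 × 0.63. The patient-level half-width is 1.96 × 0.0742 = 14.5 percentage points; the 2-df half-width is 4.30 × 1.15 × 0.0742 ≈ 36.8 points, 2.5 times wider.
- m = 56, ICC 0.01: 11.3 against 31.0 points, 2.7 times wider.
- ICC 0.05: about 3.6 times wider (m = 34) and 4.25 times wider (m = 56).

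**Power of the 2-df analysis for 17% versus 37%** (noncentral t, SE inflated by √DE):

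| ICC | m = 34 | m = 56 |
|---|---|---|
| 0 | 33% | 47% |
| 0.01 | 27% | 35% |
| 0.02 | 23% | 28% |
| 0.05 | 17% | 19% |

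**Randomisation floor.** Four PHCUs split two and two give C(4,2) = 6 allocations. Mirror-image allocations give the same absolute difference, so the smallest two-sided permutation p-value is 2/6 = 0.33.

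**The case against.** **A condensed article may be silent on random effects.** Saying that a model accounts for repeated measurements does not exclude a PHCU effect, and an unseen analysis plan might include one. This lowers certainty but does not carry the point. The article names the correlation its models are built to handle, lists covariates without PHCU, and sizes the trial with no clustering allowance. Design and analysis sections agree on a patient-level approach.

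**The t-tests may be only baseline checks.** Their sentence follows one on baseline comparability. That sentence, however, refers to variables at 0, 24 and 32 weeks, so the reading is open. The point does not depend on it, because the mixed-model sentence is enough.

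**The error rates come from a crude test.** The planned models include baseline values and covariates, among them distance to the sports facility, which could lower the residual ICC. This stands as a caveat: the percentages are illustrations, and the relevant ICC is the one left after adjustment. Covariates do not replace a PHCU term, and the 2 df remain.

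**Inflation is small at a small ICC.** True at 0.005 (6.9% and 8.3%). Even at ICC 0, though, a PHCU-level interval is 4.30/1.96 = 2.2 times wider than the patient-level one.

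**A random intercept can miss the problem.** If week 0 stays as an outcome and the effect is read as arm by time, a PHCU intercept largely cancels. The article enters baseline as a covariate, so the intercept does its work; the condition should be written down. A PHCU variance estimated at zero makes the 2-df test conservative, not liberal.

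**Class clustering is not settled.** The article does not say whether classes mix patients from the two intervention PHCUs. If they do, the two PHCU summaries are not fully independent. This limitation stands.

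**Conclusion.** The analysis is wrong as written and must be fixed before any between-arm test is reported. The stated models handle correlation within a patient but not within the randomised unit. Over assumed ICCs of 0.01 to 0.05, with equal PHCU sizes, actual type I error is about 9 to 23% at 34 patients per PHCU and 12 to 32% at 56. Below that range the inflation is modest. What does not depend on the assumed ICC is that the randomisation supports only 2 degrees of freedom and a permutation p-value no smaller than 0.33, so patient-level p-values and intervals claim a precision that two PHCUs per arm cannot give.

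**What to change.** Make PHCU a level in every analysis that compares the arms, and name one of these as primary:

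1. **Two-stage analysis (simplest).** Adjust at patient level for baseline and the chosen covariates without an arm term, summarise by PHCU, and compare the four summaries by a t-test on 2 df.
2. **Mixed model.** Add a PHCU random intercept to the patient-level model, with the week 0 value as a covariate and between-within degrees of freedom fixed at 2. Ordinary large-sample inference is not adequate with four PHCUs. If week 0 is kept as an outcome, a PHCU-by-time term is needed as well.

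Drop the unclustered t-test, analysis of variance and Mann–Whitney comparisons between arms. Report the observed ICC with its uncertainty. Record exercise class and whether classes mix PHCUs, and state this as a limitation or examine it in a sensitivity analysis. State in advance that with two PHCUs per arm the result is an estimate with a wide interval and not a confirmatory test.

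The change needs only revised wording and a few lines of code, with no new data. Its real cost is that intervals become about 2.5 to 4 times wider over the assumed ICC range and the power of a valid test is 17 to 35%, against the 90% stated. No analysis wording removes that; a confirmatory claim would need more PHCUs per arm.
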